### Outcomes and measures

#### Primary outcome

The primary outcome for this study is change in past 4-week suicidal ideation at T3 and T4 when compared to T2, assessed via the SIDAS [45]. The SIDAS is designed to screen individuals in the community for presence of suicidal thoughts and assess the severity of these thoughts. It comprises five items, each targeting an attribute of suicidal thoughts: frequency, controllability, closeness to attempt, level of distress associated with the thoughts and impact on daily functioning. Responses are measured on a 10-point scale. Total SIDAS scores are calculated as the sum of the five items, with controllability reverse scored (10 = 0, 9 = 1,…, 0 = 10), with total scale scores ranging from 0 to 50. Items are coded so that a higher total score reflects more severe suicidal thoughts.

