### Sample size and power calculation

The critical power calculation for this study relates to Component 2 (RCT of Reframe IT). The primary outcome variable for Reframe IT is reduced suicidal ideation, measured by the SIDAS, at 24 weeks (T4), in comparison to SIDAS scores at Time 2.

The Suicidal Ideation Questionnaire (SIQ) [61, 62] was used in the Reframe IT pilot study [33]. The SIQ and SIDAS are both continuous self-report measures of the frequency of cognitions related to suicide within the past month, with higher scores corresponding to more frequent and severe suicidal ideation. The range of the SIDAS is 0–50 and the range of the SIQ is 0–180. A SIDAS score of 1 or more indicates “risk for suicide”, whereas a SIQ score of 41 or more indicates “need for further evaluation of psychopathology”. As the SIQ licence is too expensive to use on a large scale, the SIDAS is being used in its place. In the absence of pilot data for the SIDAS, the power calculation is based on the SIQ. This can be reasonably justified given the similarities between the measures and their cut-offs and has been calculated in consultation with the study statistician.

In the Reframe IT pilot study, there were three time points of data collection (corresponding to T2, T3, and T4 as labelled in the current study). The mean reduction in SIQ between T1 and T3 (i.e. corresponding to T2 and T4 in the present study) for the pilot control group was 61.6 points (SD = 42.3) and for the pilot intervention group this was 47.1 points (SD = 41.6). The difference between these two reductions was 14.5 points. We also observed an intra-class correlation of 0.023 within schools, which gives a design effect of 1.1. Using these data, and making the conservative assumption that there is no correlation between SIQ scores within individuals over time, a 5% significance level and 80% power means that a sample size of 134 per arm (268 in total) is required.

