Based on pilot data, and in consideration of the self-reported nature of the data collected, we estimate that, to recruit the required 268 students, we need to screen 4020 students (see Fig. 1). This is based on 20% drop-out rate among those who are classed as high-risk, consenting, and randomised; 33% of those identified as high-risk consenting to participate in the trial and being randomised (335 consenting and randomised, and analysed on an intention-to-treat basis); and 25% of the total sample endorsing suicidal ideation within the past month (1005 students). There are 141 mainstream secondary schools in the region and approximately 140 year 10 students per school. It is therefore estimated that approximately 29 schools will be recruited in total, although this number may fluctuate depending on the rate of student recruitment. Schools will be recruited in batches throughout the project. If the target sample size is reached before the 29 schools have been recruited, no further schools will be recruited. Similarly, if we recruit the target 29 schools but fail to recruit the required number of participants, more schools will be invited to participate. In the event that we struggle to meet the recruitment target, or if it is unfeasible to recruit year 10 students at a particular school, year 11 students may also be recruited.

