### Randomisation and treatment allocation

Students who consent to participate in Component 2 will be randomised to the intervention group (Reframe IT plus TAU) or to the control group (TAU only) using block randomisation with varying block sizes and stratified by school. The allocation ratio will be 1:1. The randomisation schedule is computer generated by independent Information Technology (IT) personnel with guidance from the study statistician. The schedule will then be implemented by a member of the study team (other than the statistician) into the REDCap database management software for allocating treatments to individual students.

A member of the study team will inform school wellbeing staff of the outcome of randomisation, and they will then inform students. With the exception of the study statistician, study team members are not blind to the treatment allocations. The study statistician will not have access to the randomisation component of the database and will not be told about the treatment allocations, and will therefore remain blinded. As the study statistician will not be involved in any aspect of this study operations other than data analysis, there are no circumstances we could foresee under which the study statistician would be required to be unblinded.

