### Statistical analyses

#### Component 1

For each continuous outcome, changes over time will be assessed using linear mixed effects modelling with school included as a random factor. This analysis will examine whether there is a trend over time and whether the trend is linear or non-linear. Change in current suicidal ideation between T1 and T2 will be assessed using the McNemar–Bowker symmetry test for nominal data.

#### Component 2

Descriptive statistics will be used to compare participant characteristics between the study arms, and to assess for any imbalance.

The analysis will adopt the intention-to-treat approach, which is to include in the analysis all participants who have been randomised and regard each participant as belonging to the randomised group concerned irrespective of protocol adherence. Difference in change in the primary outcome of SIDAS score between the treatment groups will be examined using linear mixed effects modelling with the treatment group as a fixed factor and school included as a random factor. Secondary outcome measures will be similarly analysed. As a secondary analysis, compliance (as measured by the number of modules completed) and other potential covariates (e.g. gender) will be accounted for.

If the amount of missing data is non-trivial, multiple imputation will be considered to handle the missing data.

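### The primary SIDAS outcome is set at T3 and T4 but powered at T4 only, and the stated Component 2 model names no student or time term; if both visits enter it together, its standard errors are wrong

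*Protocol article*

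**What the plan says.** Three sections of the Protocol article bear on the primary comparison for Reframe IT.

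- The section that defines the main endpoint reads: "The primary outcome for this study is change in past 4-week suicidal ideation at T3 and T4 when compared to T2, assessed via the SIDAS". Each randomised student therefore has two primary changes, both measured from the same T2 score.
- Sample size and power calculation: the trial is sized on a fall in suicidal thoughts, "measured by the SIDAS, at 24 weeks (T4), in comparison to SIDAS scores at Time 2". This is one change per student.
- Statistical analyses, Component 2: "Difference in change in the primary outcome of SIDAS score between the treatment groups" is to be examined "using linear mixed effects modelling with the treatment group as a fixed factor and school included as a random factor". Secondary outcomes are to be handled in a similar way. PHQ-9, HSC and NPOQ are also defined at both T3 and T4 against T2.

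Allocation is by individual student, "using block randomisation with varying block sizes and stratified by school. The allocation ratio will be 1:1". The Component 1 paragraph likewise names only school as a random factor, for an analysis of trend over time that must have several rows per student.

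**The concern.** The model sentence is not silent on dependence. It names the school level, where the pilot intra-class correlation was 0.023, and does not name the student level, where repeated SIDAS scores will be much more alike. Read together with an outcome set at two visits, it permits a fit in which a student's repeated scores are treated as unrelated once school is accounted for. The p-value and confidence interval of the main comparison would then be wrong, and the direction would depend on how the rows were laid out. With no time or arm-by-time term, a joint fit would also estimate an average over T3 and T4 rather than the T4 effect on which the trial was sized.

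**Working it through.** **Inputs.** From the article: 14.5 SIQ points to detect, SDs 42.3 and 41.6, 5% significance, 80% power, 134 per arm, 335 randomised for 268, ICC 0.023, about 29 schools. The article gives no within-student SIDAS correlation. I write ρ for the correlation between scores at two visits and r for the correlation between the T3 and T4 changes, and show 0.3 to 0.7 as an assumed range.

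**The plan's own figure.** For one T4-minus-T2 change per student, two-sided 5%, n = 2(1.960 + 0.842)²·SD²/14.5². SD 42.3 gives 134 per arm; the pooled SD of 41.95 gives 132. So the stated 134 matches a single change per student at T4. It appears only when the stated design effect of 1.1 is left out (145 to 148 with it), which is a separate matter.

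**Layout A: T3 and T4 changes stacked, school the only random term.** With equal variances and equal correlations, the covariance of the two changes is σ²(1 − ρ) and each variance is 2σ²(1 − ρ). So r = 0.5 whatever ρ is, because both changes share T2. It exceeds 0.5 if T3 and T4 correlate more strongly with each other than with T2. The variance of a student's mean change is proportional to (1 + r)/2; the model assumes 1/2. Hence true SE / model SE = √(1 + r), and type I error = 2[1 − Φ(1.96/√(1 + r))].

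**Layout B: T2, T3 and T4 scores as rows, arm-by-time contrast at T4, no student effect.** The true variance is proportional to 2(1 − ρ); the model assumes 2. Hence true SE / model SE = √(1 − ρ).

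**Layout C: one change per student per model** (T4 minus T2 alone, or T3 and T4 in separate models). There is no repeated row, and a school effect is sufficient.

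| Correlation (r in A, ρ in B) | A: SE ratio | A: type I error | B: SE ratio | B: type I error |
|---|---|---|---|---|
| 0.3 | 1.14 | 8.6% | 0.84 | 1.9% |
| 0.5 | 1.22 | 11.0% | 0.71 | 0.6% |
| 0.7 | 1.30 | 13.3% | 0.55 | 0.03% |

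Null simulations (400 runs each, 29 schools of 9 students, ICC 0.023, no missing data, Monte Carlo SE about 1.1 points at 5%) at ρ = 0.3 and 0.6 gave 11.5% and 10.8% for A, 2.8% and 0.0% for B, and 6.0% and 3.8% for C. These agree with the formulas and with nominal error under C.

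**Power under B at ρ = 0.5.** If the pilot SDs are SDs of change, the planned SE is the true one, and 80% power falls to Φ(2.80 − 1.96 × 1.414) = Φ(0.03), about 51%. If instead planning really set the correlation to zero, the planned SE is the model's SE, and power is Φ((2.80 − 1.96) × 1.414) = Φ(1.19), about 88%. The article supports both starting points, so no single power loss can be claimed.

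**What C gives up.** At one visit with equal variances, raw change has variance 2σ²(1 − ρ) and a T2-adjusted score has σ²(1 − ρ²). The ratio is (1 + ρ)/2, that is 0.65, 0.75 and 0.85 at ρ = 0.3, 0.5 and 0.7. A T4 change score also needs T2 and T4. With the planned "20% drop-out rate among those who are classed as high-risk, consenting, and randomised", 335 − 268 = 67 students are expected to be lost. How many of them would be seen at T3 is not stated.

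**The case against.** The best defence is that the sentence describes a valid analysis. It concerns a difference in change, has arm as its single named fixed factor and has no time term, which is how one would describe one change score per student. The sample size section names that score, T4 against T2. Fitting T3 and T4 changes in two separate models also matches the outcome definition, uses T3 and keeps nominal error for each test. In addition, a condensed article may leave covariance structure to the full protocol or analysis plan, and multiple imputation is mentioned for non-trivial missing data.

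Most of this stands. A reader might infer that school is the only random term and that the trial's error bars are therefore wrong. The documents do not support that: school is the only random factor named, but it is not said to be exclusive, and nothing says that T3 and T4 enter one model. A reader might also quote the 51% power figure as a finding. It depends on taking the pilot SDs as change-score SDs, whereas the sample size section says it was "making the conservative assumption that there is no correlation between SIQ scores within individuals over time".

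The defence does not remove the mismatch between sections. T4 alone does not match the two-visit outcome, and two separate models give two primary tests where the sample size section names one. Nor is the article merely silent on structure: it states a model, and the Component 1 paragraph names the same random factor for data that are certainly repeated.

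**Conclusion.** The point holds conditionally. The outcome and sample size sections name different primary time points, and the stated model does not fit the two-visit outcome if both visits enter it together. In that case type I error is about 11% at r = 0.5 (8.6% to 13.3% over 0.3 to 0.7) with stacked changes, or intervals are too wide by 1/√(1 − ρ), a factor of 1.41 at ρ = 0.5, with raw scores and arm-by-time. With one change score per student per model there is no error in the test, only lost precision and, without imputation, lost students. The figures assume equal variances and an assumed range of correlations; the link from ρ to r = 0.5 also assumes equal correlations between visits. Because the joint-modelling reading is not established, this is best treated as a cost-free improvement to the text and not as a demonstrated error in the primary analysis.

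**What to change.** 1. Reconcile the Primary outcome and Sample size sections on one primary time point.
2. Replace the Component 2 model sentence with a repeated-measures linear mixed model on T3 and T4 SIDAS. Include arm, time, arm-by-time, T2 SIDAS and a school effect, with a student random effect or unstructured within-student covariance. Take the primary contrast at the designated time point.
3. State how missing T2 scores are handled, for example by imputation. The adjusted model would otherwise drop those students, which conflicts with including everyone randomised. Students seen at T3 but lost by T4 then contribute under a missing-at-random assumption.
4. Use the same structure for PHQ-9, HSC and NPOQ.

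The cost is wording only. All the scores are already scheduled, so no new data are needed. The change should be made before analysis, so that the choice of layout cannot be made after the results are seen.

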### Procedure

Participants will be assessed at four time-points: baseline (T1), 2 weeks post-baseline (T2), 12 weeks post-baseline (T3), and 24 weeks post-baseline (T4). The T2 assessment will be completed immediately following participation in the safeTALK workshops, and T3 at the end of the Reframe IT intervention period (see Table 1).

**Table 1 Tab1:** Schedule of assessments and interventions

Time point		Study period				
	− T1	T1	T2		T3	T4
		Baseline Week 1	Week 3	Weeks 4–12	Week 12	Week 24

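### The stated primary model compares change in SIDAS by arm and school and names no starting SIDAS score as a covariate, forgoing about 2 to 18 points of power, depending on a correlation the protocol does not report

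*Protocol article*

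**What the plan says.** The primary outcome section defines the outcome as "change in past 4-week suicidal ideation at T3 and T4 when compared to T2, assessed via the SIDAS". Under Statistical analyses, Component 2, "Difference in change in the primary outcome of SIDAS score between the treatment groups" is to be examined by "linear mixed effects modelling with the treatment group as a fixed factor and school included as a random factor". The next sentences carry this to the other scales ("Secondary outcome measures will be similarly analysed") and place covariates in a later step: "As a secondary analysis, compliance (as measured by the number of modules completed) and other potential covariates (e.g. gender) will be accounted for". A starting SIDAS score is named in neither place.

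Table 1 shows SIDAS, PHQ-9, HSC and NPOQ collected at T1, T2, T3 and T4. In this protocol baseline means T1; T2 is two weeks later, straight after the safeTALK workshop. Randomisation is stratified by school only. Entry to Component 2 depends on the SIDAS score at the baseline assessment.

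The sample size section takes its inputs from SIQ pilot data and describes itself as "making the conservative assumption that there is no correlation between SIQ scores within individuals over time".

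**The concern.** Subtracting a starting score is not the same as adjusting for it. A raw change score fixes the slope of follow-up on the starting value at 1. The variance-minimising slope, with equal variances at both visits, is the within-person correlation, which is below 1. The change score therefore carries noise from the starting measurement that a covariate would remove.

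Two things are at stake. First, precision on the one comparison the trial was sized for, and on three secondary scales, is left unused although the data are already collected. Second, starting severity is not a stratification factor, so chance imbalance in it feeds into an unadjusted change estimate: the arm that happens to start higher is expected to fall further. The protocol plans descriptive statistics to look for imbalance, but the primary model as stated has no term that would respond to it.

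**Working it through.** **Inputs (Sample size and power calculation).** Difference in mean reduction 14.5 ("The difference between these two reductions was 14.5 points"; only its size is used here); SD of the reduction 42.3 in the pilot control group and 41.6 in the intervention group; 5% significance, 80% power, 134 per arm; within-person correlation assumed to be 0, with no observed value given.

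**Step 1: reproduce the plan's figure.** For two means, n per arm = 2 × [SD × (1.960 + 0.842) / difference]². With SD 42.3: 2 × (42.3 × 2.802 / 14.5)² = 133.6, so 134. The pooled SD of 41.95 gives 132. The stated size is therefore matched by a two-sided, unadjusted change-score comparison with 42.3 as the SD of change and no design effect. Reading the SDs as single-visit SDs with zero correlation would give 263 per arm, which does not match.

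**Step 2: variance ratio.** Let s² be the variance at each visit and rho the correlation between starting and follow-up score.

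- Change score: 2s²(1 − rho)
- Follow-up score adjusted for the starting score: s²(1 − rho²)
- Ratio, adjusted to change: (1 + rho)/2, below 1 for every rho below 1

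**Step 3: power at 134 per arm.** Noncentral t, difference 14.5, SD = 42.3 × √ratio for the adjusted analysis. The unadjusted change score gives 79.8%.

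| rho | ratio | SD | power, adjusted | gain (points) |
|---|---|---|---|---|
| 0 (plan's assumption) | 0.50 | 29.9 | 97.7% | 17.9 |
| 0.3 | 0.65 | 34.1 | 93.4% | 13.6 |
| 0.5 | 0.75 | 36.6 | 89.8% | 10.0 |
| 0.7 | 0.85 | 39.0 | 85.8% | 6.0 |
| 0.8 | 0.90 | 40.1 | 83.8% | 4.0 |
| 0.9 | 0.95 | 41.2 | 81.8% | 2.0 |

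All values of rho except 0 are assumed. Applying the plan's design effect of 1.1 (n = 134/1.1 per arm) gives 75.9% unadjusted, against 96.5% at rho = 0, 86.8% at 0.5 and 82.4% at 0.7. The pattern is the same.

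**Step 4: which starting score.** The Table 1 note places Reframe IT consent between T1 and T2, before randomisation. The Procedure section describes randomisation before it turns to the workshop and T2, and the randomisation section has school staff tell students their allocation. T2 may therefore be a self-report made after randomisation with the allocation known. T1 is measured before randomisation, and every randomised student has it because eligibility rests on it.

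If T1 is the covariate and the comparator is change from T2, the ratio becomes (1 − r₁²) / [2(1 − r₂)], where r₁ is the T1-to-follow-up and r₂ the T2-to-follow-up correlation. It equals (1 + rho)/2 when r₁ = r₂ = rho. If r₁ is lower, the gain shrinks. At r₂ = 0.5 there is a gain for any non-zero r₁ (1 − r₁² against 1). At r₂ = 0.7 there is a gain only if r₁ exceeds √(1 − 0.6) = 0.63.

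Adding T1 to the existing T4-minus-T2 change is not a substitute. Its covariance with that change is s²(r₁ − r₁₂), where r₁₂ is the T1-to-T2 correlation, and this is zero when all visit pairs are equally correlated.

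**The case against.** The strongest objection is that this is a condensed article whose analysis plan is not shown. The model is one sentence; it omits time and any participant-level term although the outcome spans T3 and T4, and the secondary covariate list is open. A reader might infer that the trial never adjusts for starting SIDAS. The text does not support that: it shows only that no such term is named in the primary model. Even so, the article does more than stay silent, because it gives the form of the outcome, lists model terms and assigns covariates to a secondary analysis. That is a stated choice that can be improved.

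A reader might also infer that the trial gives up planned power, and by a single figure such as 10 points. Neither follows. The 134 per arm reproduces for the unadjusted comparison, so sizing and analysis agree; any shortfall from the 1.1 design effect is a separate sizing matter. Ten points needs rho near 0.5, a value found nowhere in the protocol.

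Finally, selection on T1 might suggest bias through regression to the mean. Regression is expected equally in both randomised arms, and some of it can occur before T2, the reference for change. The estimate is unbiased over randomisation; only sensitivity to chance imbalance remains.

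**Conclusion.** The point holds as a matter of efficiency. The primary Component 2 model, as stated, is a valid but avoidably inefficient change-score comparison, and the same form is carried to PHQ-9, HSC and NPOQ. With equal variances and a common correlation across visits, the direction holds for any rho below 1. The size is about 18 points of power at the plan's own zero correlation, falling to about 2 points at rho = 0.9.

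The result rests on SIQ pilot values standing in for SIDAS, on 42.3 being an SD of change (the reading that reproduces 134), and, for T1 adjustment, on T1 predicting follow-up about as well as T2 does. Because students are selected on T1, the spread of T1 scores among those randomised may be narrower than at later visits. That is a reason to treat the upper figures as indicative and to keep the change-score analysis alongside.

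**What to change.** In Statistical analyses, Component 2, state the primary model as follows: SIDAS score at T3 and T4 as the outcome; treatment group, time and group by time as fixed effects; T1 SIDAS score as a fixed covariate; school as a random factor. Use the same form for PHQ-9, HSC and NPOQ, each with its own T1 score. Add the T2 score as a covariate only if the trial team confirms that T2 precedes randomisation. Do not simply add T1 to the T4-minus-T2 change. Keep the unadjusted change-score comparison as a sensitivity analysis.

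The cost is a sentence or two of wording, settled before unblinding, and about one degree of freedom. It needs no new data or participants. The treatment effect would be reported as a difference in adjusted follow-up score rather than in change from T2, so the wording of the primary outcome should be aligned with it.

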#### Reframe IT

The Reframe IT intervention has been described elsewhere [33–35]. In brief, it comprises eight 20-min self-guided CBT modules. It follows the stories of two young people who make video diaries about their day-to-day life and their experience of feeling suicidal. An adult “host” character guides the user through the module and activities. Each module contains two “activities” based on standard CBT exercises. Users progress sequentially through the content, with modules automatically unlocked when the preceding module is complete. There is also a message board through which the participant can communicate with a moderator, a mood diary function, and a series of factsheets and information on local and national helplines and services.

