#### Control intervention

Participants randomised to the control group will receive TAU (e.g. from the school counsellor or external mental health services). The specific nature of TAU will be determined by the wellbeing team at each school. Although this may result in variability in treatment type between sites, the use of TAU as a comparator will facilitate an evaluation of whether receipt of the Reframe IT intervention is associated with improvement over current practice [47]. The wellbeing team at each school will be asked to record what TAU comprised for each student.

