#### Procedures for monitoring compliance with the intervention

To monitor compliance with safeTALK, a question will be included in the T2 questionnaire asking if participants were present for the entire safeTALK workshop. If participants respond “no”, they will be asked to indicate how much of the session they were present for. A researcher will be present for the delivery of safeTALK and will keep a record of any students who leave the session prematurely, including the amount of time and number of workshop modules the participant was present for.

Compliance with the screening intervention will be determined by assessing whether or not participants complete the suicide risk questions.

Participants’ use of Reframe IT (including a number of log-ins, number of modules completed, and responses to activities) will be automatically recorded by the system. At the conclusion of the study, usage statistics will be evaluated.

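### Modules completed, recorded after randomisation and zero by design in controls, is listed as a covariate, so the secondary Component 2 analysis estimates neither the treatment effect nor the effect in users

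*Protocol article*

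**What the plan says.** Under Statistical analyses, Component 2, the protocol article makes intention-to-treat primary: the analysis will "regard each participant as belonging to the randomised group concerned irrespective of protocol adherence". The primary model is "linear mixed effects modelling with the treatment group as a fixed factor and school included as a random factor", applied to change in SIDAS. The compliance sentence follows: "As a secondary analysis, compliance (as measured by the number of modules completed) and other potential covariates (e.g. gender) will be accounted for". The word "other" in it puts modules completed in the same list as gender.

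Three other sections bear on this variable:

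- **Reframe IT** describes the programme: "it comprises eight 20-min self-guided CBT modules". The same section lists a moderated message board, a mood diary and factsheets. Procedure places the modules between T2 and T3, after randomisation.
- **Randomisation and treatment allocation** and **Control intervention** give controls treatment as usual only, so a control student has no modules to complete.
- **Randomisation and treatment allocation** also says that the statistician "will not be told about the treatment allocations, and will therefore remain blinded", and that no reason to unblind is foreseen.

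The article names no complier-average, instrumental-variable or other causal estimand for compliance.

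**The concern.** Gender is fixed before randomisation, so adjusting for it leaves the randomised comparison intact. Modules completed is a consequence of allocation. It varies in one arm only, and it may share causes with the outcome. The article itself gives one route: under the discontinuation criteria, a student stops Reframe IT if it interferes with managing risk of harm.

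With both terms in the model, the module slope is learned entirely from the intervention arm. The arm coefficient then compares controls with intervention students projected to zero modules. Anything that works through the modules is subtracted out, and any link between use and prognosis is loaded onto the arm term with the opposite sign.

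At stake is the answer to whether Reframe IT helps the students who use it. The modules are self-guided and unlock in sequence, so partial use is plausible and the question will matter.

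**Working it through.** The article gives no figure for this analysis, so there is none to reproduce. It supplies 134 per arm, eight modules, controls on usual treatment only, and the 14.5-point pilot difference used in the sample size section. Adherence, its relation to prognosis and the effect per module are assumptions. School clustering is left out.

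**Algebra.** Because modules are zero in controls, least squares gives

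arm coefficient = intention-to-treat difference - (module slope x mean modules in the intervention arm).

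If the whole effect acts through modules and use is unrelated to prognosis, the subtracted term equals the whole effect and the arm coefficient is 0. If use is related to prognosis, the slope is wrong and the error is multiplied by the mean module count.

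**First set (SIDAS-like score, negative = benefit).** Severity S is standard normal. Modules = 4.5 - S + N(0, 2.3), rounded and held to 0-8. Follow-up score = 6S + N(0, 8) - 0.9 x modules. T2 score = 6S + N(0, 8). Mean modules are 4.4 and the correlation of S with modules is -0.39. True intention-to-treat effect: -0.9 x 4.4 = -4.0.

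| Outcome analysed | Module slope (truth -0.9) | Arm coefficient |
|---|---|---|
| Follow-up score alone | -1.92 | +4.57 |
| Follow-up score, T2 score as covariate | about -1.6 | +3.0 |
| Change from T2, severity carried over fully | -0.89 | -0.04 |
| Change from T2, half of severity gone by follow-up | -0.38 | -2.3 |

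The identity agrees to rounding. For the third row, -4.0 + 0.89 x 4.4 = -0.1; for the fourth, -4.0 + 0.38 x 4.4 = -2.3. The slope in the second row is backed out as (-4.0 - 3.0) / 4.4 = -1.6. On the follow-up score alone, a weaker correlation of -0.21 gives +2.6, and no correlation gives about 0.

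**Second set (reduction in score, positive = benefit, SD 42).** Here a latent factor drives use and has correlation c with the reduction itself. Mean modules are 4.28. The size 14.5 is borrowed from the article as a benefit of Reframe IT, for scale only. Arm coefficient with modules in the model:

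| True effect | c = -0.5 | -0.3 | 0 | +0.3 | +0.5 |
|---|---|---|---|---|---|
| 14.5, acting through modules | +31.4 | +18.9 | -0.05 | -18.9 | -31.3 |
| 14.5, the same at any module count | +45.8 | +33.3 | +14.7 | -4.2 | -16.9 |
| None | +31.5 | +18.6 | +0.1 | -18.7 | -31.5 |

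The standard error is about 8. With no true effect, the arm term is significant in 64% and 63% of trials at c = -0.3 and +0.3, against 5% at c = 0. One cell with a real effect is unbiased: use unrelated to outcome, and an effect that does not depend on modules.

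**Randomised arm as instrument.** The estimate is the intention-to-treat difference divided by mean modules. In the second set, where the effect acts through modules, the truth is 14.5 / 4.28 = 3.4 per module and the estimates were 3.36 to 3.42 at every c. This relies on allocation acting only through modules. In the first set, give half of the effect a direct route (-2.0) and leave -0.45 per module. The total is still about -2.0 - 0.45 x 4.4 = -4.0, and the instrument returned -0.89 per module, twice the truth.

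**The case against.** **The text fixes no model.** The sentence says only that compliance is to be accounted for. A complier analysis would also do that, and an analysis plan that is not shown may specify one. This stands as a limit on the claim. But the sentence does name the variable and groups it with gender as a covariate, and a valid complier analysis would have to depart from that wording.

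**Apparent harm.** From the +4.57, a reader might infer that the planned analysis will make a helpful programme look harmful. The documents do not support this. The outcome is change from T2. When stable severity links use to outcome, the change score removes much of that link, and the arm coefficient is about 0 or -2.3: adjusted away or attenuated, not reversed. In that set, reversal needs the follow-up score as outcome. The second set shows reversal on a change outcome too, but only if use tracks the amount of change with a particular sign. The documents give no information on that.

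**The instrument has its own assumption.** This is correct. The message board, mood diary and factsheets are routes other than modules, so a per-module estimate is the less credible target.

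**Blinding.** A reader might infer that module counts reveal every student's arm. They do not: intervention students who never start also score zero (5.5% in the first set). The article also defers evaluation of usage statistics to the end of the study, which covers part of the timing. What remains is that any non-zero count identifies the intervention arm.

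**Conclusion.** The point holds for what the article states. Modules completed is a post-randomisation variable, zero by design in controls, and does not belong in a covariate list beside gender. That controls have no modules is inferred from their allocation to usual treatment only; sharing of access within a school could breach it slightly.

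The resulting arm coefficient is neither the treatment effect nor the effect in users. The structural fault does not depend on the simulations; its size does. Against a true -4.0, the first set gave -2.3 to about 0 on change scores, and +3.0 to +4.6 on follow-up scores at the stronger assumed correlation. The direction of any further bias cannot be known from the documents.

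It would be wrong to infer that the trial's main conclusion is at risk: the primary intention-to-treat analysis and the sample size are untouched. This should be corrected, but it concerns a secondary analysis.

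**What to change.** - Remove modules completed from the covariate list. Keep gender and other pre-randomisation covariates in a separate adjusted model.
- Define the compliance analysis as a complier average causal effect with randomised arm as instrument, preferably for a minimum use of Reframe IT stated in advance, adjusted for T2 SIDAS and school.
- State the exclusion assumption. For a use threshold, allocation must have no effect in students below it. For a per-module estimate, allocation must act through modules alone, which the message board, mood diary and factsheets make less credible.
- Release module data to the statistician only after the primary analysis is locked, so that the compliance analysis is consistent with the blinding statement.

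The cost is a few sentences, one standard analysis and a wider interval than simple covariate adjustment gives. Recruitment and data collection do not change, since the platform already logs module use.
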